#### Survey development

Questionnaires are developed by the research team and tested and adjusted in correspondence with the community advisory group. The research team will make the final decision. Questionnaires will be developed in Dutch and translated into French, Spanish and English, as well as other languages if this appears necessary after the community mapping study. Because of recruitment taking place in a variety of non-research settings, we opted for a relatively short questionnaire to fill in on the spot, as well as a follow-up questionnaire with additional questions which is sent to the participants later by email. The main questionnaire (S1 Appendix) will include demographic questions, questions concerning medical history and questions regarding sexual and drug-using risk behavior and the use of relevant medicines (pre-exposure prophylaxis, PrEP). The follow-up questionnaire (S2 Appendix) will be sent to participants by email no longer than two weeks after filling in the main questionnaire and donating the oral fluid sample. This questionnaire will include additional demographic variables (marital status, living situation, education, financial situation), transgender specific questions (gender affirming hormone use, surgery), sexual health and satisfaction and additional questions regarding risk behavior (drug use, condom use, reasons to engage in transactional sex) and confounding factors (blood or organ transfusion, endoscopic examination).

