#### Outcome of interest

An HIV diagnostic orientation test will be used to assess the presence of antibodies in an oral fluid sample as described by Platteau et al. [44] and Loos et al. [38]. The participants will receive a sampling kit identified with a unique sample code which will be linked to the anonymous behavioral questionnaire, and they will take the oral fluid aliquot following the instructions.

Oral fluid is collected and tested for the presence of HIV antibodies with the DPP HIV1/2 Assay (Chembio Diagnostic Systems, Inc). This assay has been previously evaluated at the Institute of Tropical Medicine by Beelaert et al. [45] and prequalified by WHO [46]. Samples are self-collected by the participants through swabbing of the outer gums with the DPP collecting device. The swab is placed into a sample buffer for shipment to the laboratory. Upon arrival in the lab, the swab is tested with the DPP HIV1/2 assay rapid test. The assay is based on a immunochromatographic test principle, with a test line which reacts positive in case of presence of HIV-antibodies and a control line, which allows detection of human IgG and serves as a built-in control for adequate sample quality and correct performance of the test. Prior to participation, participant registers on the website via an account. In this procedure, the participant provides both an email address and cell phone number. As soon as the result is available, participant receives an email indicating that the test result is accessible. Project collaborators monitor whether participants picked up their test result. In case a participant does not pick up a negative test result, he/she will receive two reminder emails. Participants with a reactive result who do not pick up their test result will be reminded several times via email and phone at a second stage. People with a reactive result, are followed-up for further confirmation testing on a blood sample according to standard-of-care HIV testing algorithm. Follow-up continues until project collaborators receive a confirmation test result. All initial analyses will be carried out by the Institute of Tropical Medicine (Antwerp, Belgium) and the outcome assessor will be blinded to the results of the behavioral questionnaire (risk factors). Confirmation tests will be executed at the Institute of Tropical Medicine, or via existing healthcare services.

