To roughly verify whether a representative sample was acquired based on the used sampling strategy, the demographic characteristics (age and gender) of the study population will be compared with the current figures on demographic composition of the TGNB population in Flanders and Belgium. However, this comparison should be interpreted with caution since the group of TGNB people who are visible in the current statistics, are probably only the tip of the iceberg

*Appropriate methods for exposure and outcome variables*. Data on exposure of interest will retrospectively be collected through self-administered questionnaires. The quality of the data is therefore determined to a large extent by the person’s ability to accurately recall past exposures to risk factors. Recall bias may result in either an underestimate or overestimate of the association between exposure and outcome. HIV positive participants are often more likely to recall exposure to risk factors than the healthy controls. Moreover, self-reporting data can also be affected by social desirability or approval since the questionnaire includes private and sensitive topics. As a consequence, the results on sexual or drug-using risk behavior could be underreported. Therefore, it is crucial to guarantee confidentiality at the time of data collection [48]. Although participants who are aware of the exact research question are much more likely to cloud their opinions and memories about the risk factors, we will not be able to blind the participants to the study hypothesis for ethical reasons and for guaranteeing a full transparent process to the community. It will also not be possible to blind the peer data collectors to the study hypothesis but they will be trained in data collection and need to adhere to a standardized operating procedure. Furthermore, the peer data collectors will be blinded to the outcome variable (HIV infection). Outcome variables will be collected from saliva analyses with objective and clear diagnostic criteria and the outcome assessors will be blinded to the results of the questionnaire.

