*Controlled for confounding*. If possible, multivariable logistic regression analysis will be used to control for all confounding factors at the same time (cfr. supra). Factors that are expected to be related with the risk factors of interest and/or HIV infection are age, gender identity, socio-economic status, medical history, ethnicity and (parent’s) country of birth (whether or not born in an HIV endemic country).

*Complete and adequate follow-up and handling missing data*. Exposure and outcome variables will be collected at the same time and no prospective follow-up of participants is foreseen in this study protocol. Of note, one can assume that the response rate for the follow-up questionnaire would be relatively low but all critical study variables are surveyed at the time of data collection. However, participants can be excluded post-test (i) when they do not belong to the target group (e.g. MSM population, residing outside Flanders or Brussels or < 18 years) based on the self-reported questionnaire or (ii) when data were wrongly entered or linked in the database. It is of note that TGNB people who refused to provide an oral fluid sample after completing the questionnaire will be included to detect any systematic difference in their characteristics and risk behavior with those who completed all steps of the study. Since TGNB people with a reactive oral fluid sample will be invited for further confirmation testing on a blood sample, there is also a risk of missing confirmed outcome data. We assure that we will do all within our capabilities to minimize the loss-to-follow-up via intensive follow-up by email and phone. At this stage, we cannot predict the loss of participants for the confirmation testing and, in first instance, both the reactive oral fluid samples as well as the confirmed HIV status will be assessed as outcome variables. For assessing the impact of the missing data on the study results, multiple imputation will be considered as method for adjusting for missing data [49].

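### The protocol does not stop the HIV result from reaching a participant before the emailed follow-up questionnaire is answered, so its supplementary risk items may be reported with knowledge of the result

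*Protocol article*

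**What the plan says.** **Result.** Under Outcome of interest: "Upon arrival in the lab, the swab is tested with the DPP HIV1/2 assay rapid test". Then: "As soon as the result is available, participant receives an email indicating that the test result is accessible". Participants who do not collect a result are reminded: two emails for a negative result, repeated email and phone contact for a reactive one.

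**Questionnaires.** Survey development splits the survey in two. The main form, completed at enrolment, holds "questions regarding sexual and drug-using risk behavior and the use of relevant medicines (pre-exposure prophylaxis, PrEP", with demographic and medical-history questions. On the second form it says: "The follow-up questionnaire (S2 Appendix) will be sent to participants by email no longer than two weeks after filling in the main questionnaire" and giving the swab. That form holds "additional questions regarding risk behavior (drug use, condom use, reasons to engage in transactional sex", and also education, financial situation and history of transfusion. No return deadline is given.

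**Bias section.** Assessment of potential study bias warns: "HIV positive participants are often more likely to recall exposure to risk factors than the healthy controls". It blinds peer data collectors to HIV status and outcome assessors to the questionnaire. On follow-up and missing data it states: "Exposure and outcome variables will be collected at the same time". It then expects a low response to the follow-up form, but holds that every critical variable is captured at enrolment.

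**The concern.** The result and the follow-up form run on separate clocks, and the article does not tie them together. A participant may open a result, possibly a first reactive one, and only then be asked about drug use and condom use. That knowledge can change recall, candour, or whether the person replies at all. The protocol names recall that depends on HIV status as a threat and blinds the field staff and the laboratory, but it does not consider what the respondent knows about the result.

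At stake are the ORs for the supplementary behaviours. Adjustment is also involved: the protocol lists socio-economic status and medical history as confounders, and part of that information sits in the follow-up form.

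**Working it through.** **1. Order of events**
- Main questionnaire: on site, it is completed in the same session as the swab. In digital clusters it is filled in on the platform, and the kit is posted out and mailed back. It precedes any study result.
- Result: exists after transport plus a rapid test. No number of days is given.
- Follow-up form: may be sent from day 0 to day 14 after the main form and swab, and answered at any time after that.

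A form sent and answered on day 0 comes before the result. A form sent on day 14 comes after it whenever transport and testing take less than 14 days. The text permits both orders. In either case, exposures placed in the follow-up form are not collected together with the outcome sample.

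**2. People affected**
- Plan's sample size, reproduced: design effect 1 + (18 − 1) × 0.08 = 2.36; 2.36 × 560 = 1321.6, stated as 1322.
- Expected cases at 3% prevalence: 1322 × 0.03 = 39.7, about 40.
- First informed by the study, using the 30% undiagnosed share cited under Sample size: 39.7 × 0.30 = 11.9, about 12.
- The other 28 or so know their status at both questionnaires, so the sequence changes nothing for them.

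**3. Possible distortion of an exposure with no effect**
Assumptions not in the documents: true exposure 25% in cases and non-cases, no false reporting of exposure, and every newly informed case opens the result before answering. With reporting sensitivity s₁ in newly informed cases and s₀ in everyone else:
- reported exposure in all cases: a = 0.25 × (0.3 s₁ + 0.7 s₀)
- reported exposure in non-cases: b = 0.25 × s₀
- OR = [a/(1 − a)] / [b/(1 − b)]

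| s₁ | s₀ | a | b | all-case OR |
|---|---|---|---|---|
| 0.95 | 0.80 | 0.2113 | 0.2000 | 1.07 |
| 0.80 | 0.50 | 0.1475 | 0.1250 | 1.21 |
| 0.80 | 0.90 | 0.2175 | 0.2250 | 0.96 |

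In the third row a reactive result suppresses reporting, and the OR falls below 1. Among the 12 newly informed cases alone, the first two rows would give 1.25 (0.2375 against 0.20) and 1.75 (0.20 against 0.125). The plan does not analyse that contrast.

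**4. Against sampling error**
With 40 cases, 8 of them exposed (20%), and about 1282 non-cases at 20%, SE(log OR) ≈ √(1/8 + 1/32 + 1/256 + 1/1026) = 0.40. The 95% interval spans a factor of about exp(1.96 × 0.40) = 2.2 either way, before clustering, weighting and follow-up non-response.

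**5. Non-response**
If newly reactive people answered half as often as others (an assumption), about 6 of the 12 would be lost. Non-response that depends on the result alone mainly costs cases; it biases an OR if it also depends on the exposure.

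**The case against.** The strongest reply is that the exposed items are secondary. The protocol treats what is surveyed at enrolment as all the critical variables, and it describes the targeted questions on drug use, condom use and sex-work reasons as additional. That stands, and it confines the point to supplementary items and some confounders. It does not rescue the simultaneity statement, which is worded without that limit.

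Second, email scheduling is operational detail that a condensed article may leave to a procedure not shown. This is fair, and two weeks is only an upper limit. The point is therefore that the protocol as written does not prevent the order.

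Third, the protocol already acknowledges recall bias by HIV status, and most of it comes from people diagnosed earlier, whom no reordering can help. This is also true. What remains is the part the study could itself add.

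A reader might infer more in three ways, none of them supported:
- That results do arrive before the form is answered. No turnaround is given, swabs must be shipped, and the form may be sent at once.
- That the risk-factor analysis as a whole is compromised. The core sexual and needle-use items precede any study result.
- That forms answered after the result should be dropped from the main analysis. Reactive results are chased harder than negative ones, so this could selectively remove the few newly diagnosed cases.

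**Conclusion.** The concern holds in a limited form. The protocol leaves open that the supplementary risk items and some confounders are answered, or not answered, with knowledge of the HIV result. Its statement that exposure and outcome are collected together is inaccurate for those items, whatever the laboratory turnaround.

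The size is modest: about 12 of about 40 cases, with an all-case OR of about 1.07 to 1.21 for a null exposure under assumed over-reporting. The direction is uncertain. This is small beside the sampling error, but it is systematic and cheap to reduce. The figures rest on 1322 participants, 3% prevalence, 30% undiagnosed, and reporting rates chosen for illustration. The two questionnaires are appendices not shown, so the placement of items is taken from the Survey development summary.

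**What to change.** - Send the follow-up link on the day of the swab or, in digital clusters, with the main questionnaire or the kit. The present upper limit of two weeks already allows this. Leave result release and follow-up of reactive results unchanged.
- Log when the follow-up form is submitted and when the result is opened. Early sending does not guarantee an early answer, so the two times are needed to see the actual order.
- Keep all forms in the main analysis of these items, and add a sensitivity analysis limited to forms submitted before the result was opened.
- Correct the simultaneity statement to say that only main-questionnaire exposures are collected together with the outcome sample.

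The cost is a change to email timing, two time stamps, one more analysis and one reworded sentence, handled through the protocol's own route for modifications. Data collection has already begun, so for forms already returned it is worth checking whether the platform kept these times.

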#### Selection and data collection procedures

After the systematic selection of clusters from the sampling frame, the investigators will randomly select and approach TGNB people from each cluster at predefined time periods. The procedure for selection of participants will be tailored to the type of setting. During consultation periods at healthcare settings, TGNB people will be randomly selected based on the available lists. At physical gatherings, TGNB people will be recruited from randomly selected tables in bars or at meetings and at parties or public events, potential respondents are randomly approached as they cross a predefined line or enter a predefined area. In digital clusters, we will also randomly select TGNB people based on available list of group/forum members. Only digital clusters that specifically targets TGNB persons will be included in this study ensuring that most of the group members potentially meet the eligibility criteria. Open and closed social media groups or online fora will be targeted. However, for closed groups permission to recruit group members is always asked to the administrators of the group. For privacy reasons, secret groups will not be included whatsoever in this study. The member lists are available in advance for selection reasons only after approval by the group administrators and the study will be briefly introduced by e.g. a wall post. The selected TGNB persons will be contacted for participation by the group administrator or peer data collector with a personal message. If (digital) networks of influencers/key informants are used, the researchers will perform the random selection based on an anonymized list and all communication will exclusively be done by the key informant. In clusters with low number of attendees (ten or less), everyone will be approached for participation.

In healthcare settings, the data will be collected by the main research team while data collection during community events and meetings will also involve peer data collectors, who will be trained and compensated for their time. One of the (peer) data collectors will approach potential participants and introduce the study, its objectives, methodology, informed consent and confidentiality. Interested participants will be invited to a separate room or area (if possible) to register in the online system, complete a structured questionnaire on a tablet and donate an oral fluid sample via a self-collection swab. Informed consent is obtained at the beginning of the questionnaire. Registering on the online platform using a personal email address is necessary to be able to check the HIV test results afterwards. If a test appears reactive, participants are linked to the HIV reference centre or other physician for a confirmation test. Community researchers will also collect data on the characteristics and the reason for refusal of those who refused participation in the study, as well as the overall number of TGNB people present during the onsite data collection.

In digital clusters, after receiving all information concerning participation in the study in a personal message, participants are guided to the online platform to fill in the questionnaire, and are asked to provide an home address to have the oral fluid test kit sent to them which they will have to send back in a prepaid envelope. If selected TGNB people are reluctant to participate, the key informant or peer data collector will make two attempts to find out the reasons for refusal. Similarly, when selected TGNB people do not respond to the invitation, the key informant or peer data collector will send one reminder notification within one week.

Although the above recruitment strategies are directed at gaining a representative study population of TGNB people, it might be difficult to include specific groups within the TGNB community [47]. For clusters in which specific hard-to-reach subpopulations gather (e.g. anarchistic TGNB activists, TGNB refugees involved in transactional sex, TGNB people of color), one can anticipate that it could be difficult to gain access as a researcher. In this case, there is the possibility to include the network of key community members (e.g. personal social media groups) who will likely already have been identified during the formative part of the study. They can act as peer recruiters, randomly contact TGNB people within their hard-to-reach network (herein defined as cluster), informing them about the study and guiding them to the online platform for data collection. In this scenario, the peer recruiters will also collect data on the characteristics and the reason for refusal of those who are reluctant to participate in the study.

#### Confidentiality and ethics

We will ensure confidentiality by using identification codes to link oral fluid tests and questionnaires. Contact information is needed for sending participants the oral fluid test in case of online recruitment, for the participant to check their testing results, and to ensure linkage to care for participants whose test was reactive. This information is linked to the identification codes in a confidential linking document which can only be consulted by the researcher responsible for data input and the person who is responsible for follow-up and linkage to care. Questionnaires will be pseudonymized upon entry in the database, except for a unique questionnaire and outcome number. The coded personal data will be used for data analysis and the results will be reported anonymously. This study was approved by the Ghent University Hospital Ethics Committee on September 17, 2020 (BC-08157; S1 and S2 Files) and July 28, 2021 (BC-08527; S3 and S4 Files). Written informed consent will be obtained at the beginning of the questionnaire. Potential protocol modifications will be approved by the ethics committee and communicated in the trials register and peer-reviewed publications (cfr. infra). Transparent study procedures that address safety and confidentiality are essential [15, 22, 24]. Hence, we will invest in strong, transparent and clear communication about the study (topic) towards the transgender community throughout all study phases, which will likely increase willingness to participate. This will involve personal communication with community members, organisers and administrators as well as broad social media communication. The data collection was started in December 2021 and anticipated date of completion is December 2022.

#### Statistical analysis plan

The proportion of HIV infection and 95% confidence interval will be estimated adjusting for clustering and unequal probability of selection. TGNB people who visited sites more frequently had a higher probability of selection in the study. (Individual) weighting factors will be calculated based on the attendance information provided by the participant to adjust for this unequal selection probability. Moreover, the probability of accepting participation and the sampling fraction (number of participants out of total number of eligible attendees at the cluster) will also be taken into account. One can expect that the real number of attendees at outreach events may deviate from the expected number used for the systematic sampling procedure. The actual number of eligible TGNB persons will always be reported in the data collection form and, if needed, weighting factors will be calculated to correct for the potential deviation in sampling probability.

Socio-demographic and geographic characteristics, sexual and drug-related risk factors of the sample will first be summarized by descriptive statistics. Logistic regression models taking into account clustering and using the sampling weights (being inversely proportional to the selection probability) will be fitted to calculate the odds ratio (OR) and 95% CI for each possible risk factor. Nine variables will be queried to map sexual risk behavior among TGNB people and three variables deal with the use of needles or risky blood contacts in the past. Depending on the number of TGNB people with HIV infection, construction of a multivariable model will be considered to estimate adjusted OR (aOR). After constructing a logistic regression model including all confounding factors (e.g. age or country of birth) that had a P<0.05 in univariate analysis, the significant risk factor(s) will then be separately added as explanatory factors to estimate aOR when deemed appropriate. Statistical analyses will be undertaken using the package ‘survey’ in RStudio to fit the above logistic regression models. Marginal models in the ‘survey’ package focus on the population mean response, averaged over all clusters, taking into account clustering and the sampling weights. Sensitivity analyses might be performed to assess the impact of e.g. potential protocol violations on the robustness of the results.

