**Methods:**

In this community-based cross-sectional study, self-identified transgender and non-binary (TGNB) people will be recruited through a two-stage time-location sampling approach. First, community settings in which TGNB people gather will be mapped to develop an accurate sampling frame. Secondly, a multistage sampling design is applied involving a stratification based on setting type (healthcare facilities vs outreach events), a selection of clusters by systematic sampling and a simple random selection of TGNB people within each cluster. Participants will complete an electronic self-reported survey to measure sociological, sexual and drug-using behaviors (risk factors) and oral fluid aliquots will be collected and tested for HIV antibodies. Logistic regression models will be used to evaluate risk factors independently associated with HIV infection. The presented study is registered at ClinicalTrials.gov (NCT04930614).

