#### Description of variables

*Gender identity*. To measure gender identity we will ask respondents to categorize themselves in one of the following categories, in order to be able to interpret the results of the study: (i) (transgender) man, (ii) (transgender) woman, (iii) non-binary or genderqueer or (iv) transvestite or cross-dresser. Whereas the two-step method—asking gender as well as sex assigned at birth—has long been advised for measuring gender identity, we will only ask for sex assigned at birth to respondents identifying as non-binary/genderqueer or transvestite/cross-dresser. Asking transgender people what sex they were assigned at birth should be avoided when not relevant, as such this is deemed unnecessary for transgender men or transgender women, but is important information for people identifying as non-binary, genderqueer, transvestite or crossdresser.

*Other socio-demographic variables*. Besides the demographic characteristics (age, city of residence, country of birth, country of birth of both parents, ethnicity, marital status, living situation, education, financial situation), variables specific for TGNB people will be surveyed (active in community, attendance to events, activities, services and digital spaces they are aware of).

*Medical history*. Past medical treatments such as blood transfusion or organ transplant may put the participant at risk of HIV infection and will be questioned as confounding factors along with access to transgender-related healthcare (gender affirming hormone therapy and surgery and/or psychosocial assistance) and sexual health history (history of STDs and HIV testing history).

*Risk behaviors*. The sexual and intravenous drug-using risk factors will be surveyed based on the time-based deferral criteria of the donor health questionnaire of Belgian Red Cross-Flanders. The donor health questionnaire primarily aims to identify risk behavior for potential transfusion‐transmissible infections. We will here implement these questions in the survey for assessing the risk factors for HIV infection: sexual risk contacts (e.g. new partners, group sex, multiple partners or transactional sex) and the use of needles for injecting drugs, hormones or silicone. In addition, to fully understand these risk-taking behaviors, more targeted questions on drug use, condom use, sex work reasons and anal intercourse will be included as well.

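### Confounders enter the adjusted model only if univariate P<0.05; with about 40 expected HIV cases this screen reflects power more than confounding, so a short pre-specified set is better

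*Protocol article*

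**What the plan says.** The Statistical analysis plan section makes any adjusted analysis conditional: "Depending on the number of TGNB people with HIV infection, construction of a multivariable model will be considered". If it is done, a confounder model is built first, "including all confounding factors (e.g. age or country of birth) that had a P<0.05 in univariate analysis". Then "the significant risk factor(s) will then be separately added as explanatory factors to estimate aOR when deemed appropriate". Nothing in the article puts a confounder into the model regardless of its P value.

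Under Assessment of potential study bias (Controlled for confounding), the article says that, if possible, "multivariable logistic regression analysis will be used to control for all confounding factors at the same time", and refers back to the analysis section. It names age, gender identity, socio-economic status, medical history, ethnicity and country of birth (own or parents'). The criterion is an expected relation to the risk factors and/or to HIV.

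Under Description of variables (Medical history), past medical treatments "will be questioned as confounding factors along with access to transgender-related healthcare" and "sexual health history (history of STDs and HIV testing history").

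The abstract promises that "Logistic regression models will be used to evaluate risk factors independently associated with HIV infection".

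**The concern.** Whether a variable confounds depends on its relation to both exposure and outcome. A univariate P value for its relation to HIV mostly tracks the number of cases. With few cases, a real confounder can easily miss P<0.05. It is then left out and the reported adjusted odds ratio carries its bias.

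The same rule puts no barrier in front of variables that lie downstream. The study's hypothesis is that sexual risk behaviour mainly determines HIV. An STD can result from that behaviour, and testing history can follow from the behaviour or from a known infection. If either is treated as a confounder and passes the screen, adjustment may remove part of the association that the study sets out to find.

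Finally, risk factors are added separately, so no adjusted odds ratio accounts for the other behaviours surveyed. The abstract's word for independence says more than that model can deliver.

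**Working it through.** **Inputs from the article (Sample size).** Prevalence 3%; 560 participants before clustering; mean cluster size 18; ICC 0.08 (range 0.03 to 0.16); 1322 participants planned.

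**The article's own figures first.**
- Expected length of the exact 95% interval at n = 560, p = 0.03: 0.0300, as stated.
- Design effect: 1 + (18 − 1) × 0.08 = 2.36. The range is 1 + 17 × 0.03 = 1.51 to 1 + 17 × 0.16 = 3.72.
- 2.36 × 560 = 1321.6, so 1322 reproduces.

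**Information available to the screen.**
- Expected cases: 1322 × 0.03 = 39.7.
- After the design effect: 39.7 / 2.36 = 16.8.

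**Chance that a true confounder passes P<0.05.** The article gives no confounder frequencies or odds ratios. Assume a binary confounder with 30% frequency and overall HIV prevalence 3%. For a given odds ratio (OR), the two risks a (confounder present) and b (absent) solve 0.3a + 0.7b = 0.03 and a(1 − b) / [b(1 − a)] = OR.
- OR 2: a = 4.56%, b = 2.33%.
- OR 3: a = 5.53%, b = 1.91%.

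The two-sided 5% score test for two proportions was enumerated exactly at effective n = 1322 / design effect:

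| Design effect | Effective n | OR 2 passes | OR 3 passes |
|---|---|---|---|
| 1 (none) | 1322 | 57% | 92% |
| 1.51 | 875 | 43% | 79% |
| 2.36 | 560 | 31% | 62% |
| 3.72 | 355 | 23% | 46% |

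At design effect 2.36, OR 1.5 passes in 15% and OR 2.5 in 48%. A normal-approximation check for OR 2 at the same design effect gives 28%, 31% and 27% at confounder frequencies of 15%, 25% and 50%, so the result does not hinge on the 30%.

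**What the screen does to the odds ratio.** An illustrative simulation (1500 runs per scenario, ordinary logistic models) assumed confounder frequency 25%, confounder OR 2, exposure frequency 20% without and 50% with the confounder, and HIV 3%. Median exposure odds ratios:

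| Effective n | True OR | Always adjusted | P<0.05 rule | Never adjusted |
|---|---|---|---|---|
| 560 | 2.0 | 2.04 | 2.16 | 2.53 |
| 560 | 1.0 | 1.02 | 1.13 | 1.26 |
| 1322 | 2.0 | 2.00 | 2.04 | 2.47 |
| 1322 | 1.0 | 0.99 | 1.04 | 1.24 |

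A study that drops the confounder reports its unadjusted estimate. The last column is the median of that estimate over all runs.

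**STD and HIV-testing history.** No arithmetic applies. The medical-history sentence joins sexual health history to items asked as confounders, and the bias section lists medical history among the factors to control. Neither place excludes variables that follow from the exposure or from the outcome.

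**The case against.** Several counter-arguments have force.

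- **Few cases need a small model.** True, and the article rightly makes adjustment conditional on case numbers. But that argues for a short set chosen in advance, not for choosing by P value.
- **The design effect of 2.36 is too harsh for this purpose.** The Sample size section itself says that the effect will be smaller for risk factors that vary within clusters. This stands, which is why the range down to no design effect is shown. Even there an OR-2 confounder is lost in about 4 of 10 studies (100% − 57% = 43%), although OR 3 is then nearly always kept.
- **Average bias is modest.** It is: 2.16 against 2.04 in the example. A reader might infer that the adjusted odds ratios will be confounded. The figures support only a liability, which is larger in those studies where the confounder drops out.
- **The two sections contradict each other.** A reader might infer this from "multivariable logistic regression analysis will be used to control for all confounding factors at the same time". But that sentence opens conditionally and points back to the analysis section, so it is a loose summary rather than a rival rule. The wording should be aligned; the conflict is mild.
- **STD and testing history will cause over-adjustment.** A reader might infer this too. The sentence can also be read as merely listing what is asked. The article's follow-up questionnaire names other confounders (transfusion, endoscopy). The Discussion says that risk exposure concerns the past 12 months, so an earlier STD may mark earlier behaviour and act as a genuine confounder. Downstream status is plausible, not shown, and entry would still require P<0.05.
- **Adding risk factors one at a time is defensible** with 17 to 40 cases and correlated behaviours. That stands. A joint or penalised model of all behaviours should not be demanded, least of all with weighted, clustered data. Only the abstract's wording needs to change.
- **The adjusted model is not the sole answer to the risk-factor objective.** Correct: an odds ratio with interval is planned for each risk factor before any adjustment.

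**Conclusion.** The screening rule is a real but limited weakness, and it is cheap to improve. On the protocol's own prevalence, sample size and design effect, a confounder with odds ratio 2 would be kept in about 31% of studies, and in 23% to 57% across design effects of 3.72 down to none. For odds ratio 3 the figure is 62% (46% to 92%). Confounder frequency and strength are assumptions, since the article states neither. The expected distortion is modest on average and larger when a confounder is dropped.

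Confidence is high on the screen itself. On STD and HIV-testing history the finding is only that the article leaves open an adjustment that may be inappropriate. On the abstract, its claim goes beyond a model that enters risk factors singly. No sample size is affected.

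**What to change.** - In the Statistical analysis plan section, replace the P<0.05 screen with a short confounder set fixed in advance from the factors that the bias section already names, for example age, gender identity and birth in an HIV-endemic country. Enter it whatever its P value and keep it small given the case count.
- Keep STD history and HIV-testing history out of the main adjusted model, and use them in a sensitivity analysis only. Make their role clear under Medical history.
- Align the Controlled for confounding paragraph with this rule.
- In the abstract, replace the claim of independent association with association after adjustment for the pre-specified confounders.

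**Cost.** This is a change of wording, with no effect on fieldwork or sample size. Intervals become somewhat wider because the covariates are always included. With age as one term, gender identity in its four categories (three terms), birthplace (one) and one exposure, the model has 1 + 3 + 1 + 1 = 6 parameters. That is 39.7 / 6 = 6.6 expected cases per parameter, or 16.8 / 6 = 2.8 after the full design effect. The set should therefore not grow beyond this, and merging sparse gender categories may be needed by a rule stated beforehand.
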